### Setting

Participants will be recruited from up to 7 GP practices and their associated physiotherapy services within one NHS PCT in the county of Cheshire, England, UK. An NHS PCT is a type of NHS Trust, part of the NHS in England, that provides primary and community services or commissions them from other providers, and is involved in commissioning secondary care [32]. There are approximately 152 PCTs in England.

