### Sample Size

#### Health care practitioners

We aim to involve a minimum of 20 GPs and 20 physiotherapists in the questionnaire surveys of phases 1 and 3, from the participating GP practices and related physiotherapy services.

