#### Patients

Scoping work in preparation for this study has provided us with information on rates of consultation and current referral pathways, by which we can assess the expected recruitment and determine the power we will have to detect clinically important changes in patient outcome. The consultation rate for back pain in local general practices ranges from 6-10% annually. We aim to invite 7 GP practices (population of approx 45,000 adults aged 18 years or over) from which we expect at least 2,700 LBP consulters per year. Previous research suggests that approximately 50% of patients will be willing to consent to completing the questionnaires [45]. Based on these figures, we anticipate that within the timeline of the study (across both phases 1 and 3), recruitment of 1000 patients should be feasible.

A difference of 2.5 points in RMDQ [37] change scores is considered to be a minimum clinically important difference [46]. We wish to test the superiority of the subgrouping for targeted treatment system (phase 3) over usual primary care (phase 1) in relation to this 2.5 point difference for those patients in the high and medium risk subgroups, and to test for non-inferiority of the new care system compared to usual care in the low risk subgroup. A weighted sample size (based on the timeline ratio of 1:2 (phase 1: phase 3) of 50 patients (phase 1) and 100 patients (phase 3) is powered at about 80% to detect a 2.5 point difference, assuming a standard deviation of 5 and using a 5% two-tailed significance level. Based on our pilot work, we expect 20% of back pain patients to be classified as at "high-risk" of poor outcome, 40% to be at "medium-risk" and 40% at "low-risk". Thus, our expected study size of 1000 patients will enable us to evaluate this clinical difference across the three risk subgroups, and has 80% power to detect a 'small' effect size of about 0.2, equivalent to a mean difference in RMDQ scores of approximately 1, over the total study population (taking into account 20% loss to follow up).

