### Data analysis

#### Health care practitioners' attitudes and behaviour and care processes

A descriptive summary of the characteristics of the participating GPs and physiotherapists will be provided. To assess differences in health care practitioners' attitudes between phase 1 and phase 3, we will compare baseline mean scores and follow-up mean scores for the self-confidence and PABs scales using matched-analyses techniques (e.g. paired t-test) based on before (phase 1) and after (phase 3) matching of scores to individual health care practitioners. The matched-analyses are based on evaluating the same health care practitioners before and after; a sensitivity analysis using unmatched approaches (e.g. unpaired t-test) will be used if the pool of practitioners in phase 3 is not exactly the same as that in phase 1. As well as providing the best estimate of the true mean difference, we will also present 95% confidence interval estimates for the difference and give p-values for the statistical tests performed. Mean changes in attitudes scores (3 questionnaires: before the quality improvement interventions, immediately after the quality improvement interventions and 12 months after the quality improvement interventions) will also be described.

Behaviour measures, relating to the two case vignettes, follow categorical or textual response formats and differences over time will be described. Health care practitioner behaviour differences between time points will also be statistically evaluated by comparing data of their actual clinical practice, e.g. health care consultations, medication prescriptions, sickness certification and patterns of referral obtained from medical record downloads for patients who consent to record reviews and from physiotherapists' case report forms. Furthermore, GP responses to the computer "pop-up" prompt on 'chronicity risk' (low; medium; high) and presence of 'yellow flags' (no; yes) will be compared to patient questionnaire responses to the subgrouping tool; the percentage agreements would be expected to be higher after the quality improvement intervention. These analyses, based on patient measures, are unmatched and will follow between-group techniques i.e. unpaired t-test, chi square test and regression methods (as described below for clinical outcomes).

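### Change in practitioners' recorded behaviour is tested as if patients were independent, although they are clustered within a limited number of GPs and physiotherapists who largely appear in both phases

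*Protocol article*

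**What the plan says.** All of this is in the Protocol article, Data analysis, under practitioners' attitudes and behaviour and care processes, unless another section is named.

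- The aim is inferential, not only descriptive: "Health care practitioner behaviour differences between time points will also be statistically evaluated by comparing data of their actual clinical practice". The data are medical record downloads for consenting patients, physiotherapists' case report forms, and the GP's pop-up risk rating compared with the patient's tool score.
- The method is fixed: "These analyses, based on patient measures, are unmatched and will follow between-group techniques i.e. unpaired t-test, chi square test and regression methods". The sentence then refers forward to the regression for clinical outcomes. That is linear or logistic regression, unadjusted and adjusted for age, gender and baseline values of key outcomes. No practitioner or practice term, random effect or cluster-robust error is given.
- Attitude scores, in the same section, are linked to the individual: "The matched-analyses are based on evaluating the same health care practitioners before and after".
- On numbers, the Sample Size section says "We aim to involve a minimum of 20 GPs and 20 physiotherapists in the questionnaire surveys of phases 1 and 3", and Setting says "Participants will be recruited from up to 7 GP practices and their associated physiotherapy services within one NHS PCT". For patients, "recruitment of 1000 patients should be feasible", with a phase 1 to phase 3 ratio of 1:2.

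**The concern.** Whether to refer, prescribe, order a test or issue a certificate is largely the practitioner's decision. The Background section says that treatment of non-specific back pain follows the experience and preferences of the individual practitioner and that practice varies. The GP intervention includes written feedback comparing each GP with colleagues in the same practice, which presupposes differences between GPs. Two patients of one GP are therefore likely to be managed more alike than two patients of different GPs.

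The protocol uses the before-after link for attitudes and drops it for the same people's actual behaviour. It recognises clustering when explaining why it did not randomise practices (Study Design), but not in the analysis.

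At stake is a key secondary objective in the Abstract: the effect on practitioners' attitudes and behaviour and on the process of care. A p-value or interval for changed referral or prescribing could be misleading, and the results are intended for clinicians, service managers and commissioners.

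**Working it through.** **Plan's own figure.** None is stated for the behaviour analyses, so there is nothing to reproduce. The power statement in Sample Size concerns the Roland-Morris score and does not bear on this point.

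**Inputs from the protocol.** Minimum 20 GPs (for the questionnaire surveys); 1000 patients; ratio 1:2.

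**Assumptions.** The documents give none of these:
- 800 patients with usable records;
- ICC within GP of 0.05 to 0.15;
- stability *c*, the correlation of a GP's own level between phases, from 0.5 to 1.0;
- 40 GPs as an alternative to 20.

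**Formula.** Suppose each GP contributes m1 patients in phase 1 and m2 in phase 3. The ratio of the true variance of the phase difference to the variance under independence is

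DE = (1 − ICC) + 2 × ICC × (1 − c) / (1/m1 + 1/m2),

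and the true size of a nominal two-sided 5% test is 2 × [1 − Φ(1.96/√DE)].

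**20 GPs, 800 records.** m1 = 800/3/20 = 13.3 and m2 = 26.7, so 1/m1 + 1/m2 = 0.075 + 0.0375 = 0.1125.

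Example with ICC 0.05 and c = 0.5: DE = 0.95 + 0.05/0.1125 = 0.95 + 0.444 = 1.39; 1.96/√1.39 = 1.66; size 9.7%.

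| Stability c | DE, ICC 0.05 | Size | DE, ICC 0.15 | Size |
|---|---|---|---|---|
| 1.0 | 0.95 | 4.4% | 0.85 | 3.4% |
| 0.9 | 1.04 | 5.5% | 1.12 | 6.4% |
| 0.8 | 1.13 | 6.5% | 1.38 | 9.6% |
| 0.5 | 1.39 | 9.7% | 2.18 | 18.5% |

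DE equals 1 only if ICC is 0 or c = 1 − 0.1125/2 = 0.944. Above that value the stated intervals are too wide, and below it too narrow.

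**Sensitivity to the assumptions, at c = 0.5.**
- 40 GPs, 800 records (1/m1 + 1/m2 = 0.225): DE 1.17 to 1.52, size 7.0% to 11.2%.
- 20 GPs, 500 records (sum 0.18): DE 1.23 to 1.68, size 7.7% to 13.1%.
- 20 GPs, 800 records, ICC only 0.01: DE 1.08, size 5.9%.

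**Simulation check.** An uncorrected chi-square test was simulated under no phase effect (20 GPs, 333 and 667 patients, assumed 30% event rate, ICC 0.05). With equal GP shares in both phases, it rejected in 4.8%, 7.7% and 12.0% of runs at c = 1, 0.8 and 0.5. The formula for the same 1000 patients gives 4.4%, 7.0% and 11.0%. When each GP's share of patients differed between phases, the rates were 9.5%, 11.9% and 16.3%. Unequal shares alone can therefore make the test too liberal even when habits are fully stable.

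No figure is given for physiotherapists, because the number of referred patients per physiotherapist is not stated.

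**The case against.** **Unmatched is literally true of the patients.** Phase 3 recruits a new cohort, and people invited in phase 1 are not re-invited. The care that patients receive is also listed as an objective in its own right. This stands as a description of the patients, but unpaired patients can still be correlated through a shared practitioner.

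**Regression is among the listed methods.** True, but the regression referred to contains no clustering term, so it shares the problem. Because the sentence names the methods with i.e., this is a stated choice and not a detail left to an analysis plan.

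**The inputs are borrowed.** This largely stands. Twenty is a survey minimum, all practising GPs at each practice are eligible, and record review needs separate permission at a rate that is not given. More GPs or fewer records shrink the effect.

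**Two stronger readings are tempting and are not supported.**
- A reader might infer that the tests must be anti-conservative, perhaps by applying the usual 1 + (m − 1) × ICC. With m = 2/0.1125 = 17.8 and ICC 0.05 that gives 1 + 16.8 × 0.05 = 1.84, which is the case of zero stability between phases. Stable practitioner effects cancel when the same GPs appear in both phases, so the inflation is usually smaller and may reverse.
- A reader might extend the criticism to the attitude scores, where "a sensitivity analysis using unmatched approaches (e.g. unpaired t-test) will be used if the pool of practitioners in phase 3" differs. There the matched analysis is the main one. The unpaired test is only an example of a sensitivity analysis, used "if the pool of practitioners in phase 3 is not exactly the same as that in phase 1". It errs on the conservative side where people overlap, and it brings back those seen only once. That is not a fault in the plan.

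**Conclusion.** The point holds for the record-based behaviour analyses. As specified, they ignore both the correlation within practitioners and the overlap of practitioners between phases, so their standard errors are right only by coincidence or if there is no practitioner effect.

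The size depends on assumptions. With 20 GPs, 800 records and ICC 0.05-0.15, true size is about 4% at stability 1.0, 6.5-10% at 0.8 and 10-18.5% at 0.5. With 40 GPs at stability 0.5 it is about 7-11%. The upper figures need a marked change in how GPs rank between phases.

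Some uneven change is plausible from the plan itself. Feedback is individual, extra meetings are optional, only some physiotherapists receive the additional 6 training days, and drift back to old habits is anticipated. The documents do not quantify any of this. These are secondary analyses, and no power statement rests on them. The correction should be made because the method is fixed in the text and is cheap to change.

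**What to change.** Replace the sentence on unmatched tests with the following plan for record-based behaviour outcomes:

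- Use a mixed model (linear or logistic) or GEE, with phase as a fixed effect and clustering on the treating practitioner.
- For GP decisions, cluster on the GP, with practice as a fixed effect. For physiotherapy data, cluster on the physiotherapist and do not nest within practice, because the physiotherapy service is organised at PCT level.
- Let the practitioner effect vary by phase (a practitioner-by-phase effect). A practitioner intercept alone would not capture uneven change.
- Apply a small-sample correction, since there may be only about 20 clusters of each kind.
- State a fallback: if the model for a binary outcome is unstable, compare practitioner-level rates before and after in a paired analysis.

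The attitude-score analysis needs no change on this account.

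**Cost.** No extra patients or visits. Practitioner identifiers must be kept in the analysis data; the GP feedback already reports recruitment and tool use per GP, so they should be obtainable. Some intervals will widen, and where habits prove very stable some may narrow slightly.

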#### Clinical outcomes for patients

The primary outcome measures of patient benefit will be back pain-related disability (measured on the RMDQ [37] and pain catastrophising (measured on the catastrophising subscale of the Coping Strategies questionnaire [38] at 6 month follow up. Primary analysis of the patient data will follow the principles of "intention to treat", to compare outcomes of patients in phase 1 (pre-intervention) to those of patients in phase 3 (post-intervention). A "per-protocol" analysis, based on the evaluation of phase 3 patients who were treated with strict adherence to the subgrouping tool allocation rule (versus all phase 1 patients) will be carried out as a secondary comparison. Estimates of treatment effects, i.e. comparative outcomes for phase 1 (pre-intervention) versus phase 3 (post-intervention), with 95% confidence intervals will be calculated using linear regression (for numerical outcomes) and logistic regression (for categorical outcomes). Analyses will be carried out both unadjusted and adjusted for baseline imbalances in certain variables i.e. age, gender and baseline values of key outcomes. Statistical adjustment is necessary as this is an observational, before and after study design, and thus open to the possibility of confounding bias; adjustment will ensure parity of key baseline patient characteristics across phases 1 and 3. Analyses will be carried out at each patient follow up time point (2 and 6 months) for primary and secondary outcome measures; the primary endpoint is 6 months. Analyses will be performed on available data, and on imputed datasets based on the method of multiple imputation [47]. We will use STATA and SPSS for the analyses.

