#### b) Patients' clinical outcomes

A consecutive sample of patients consulting with LBP at each participating practice will be recruited in phase 1 for a period of up to 6 months. As each patient consults with LBP at one of the participating GP practices and is assessed, if their GP enters a previously validated back pain Read Code [2] to indicate the reason for consultation as non-specific LBP, a "pop-up" computer prompt will remind them that the patient is eligible to be invited to participate in the IMPaCT Back study. The GP will inform the patient about the study and ask them if they are willing to receive further information by post. On the same computer pop-up screen the GP will record whether the patient is willing to receive further information about the study, in addition to recording their own clinical impression of the patient's risk of poor outcome (low, medium or high risk of poor outcome). The GP will be able to "opt out" of the computer screen pop-up if they consider the patient not eligible for the study. In phase 1, all patients will receive usual primary care, with referral to other services (including physiotherapy) as usual. There will be no subgrouping for targeted treatment in phase 1, or any specific training or additional resources for assessing and managing LBP patients.

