### The sub-grouping tools and targeted treatment approaches

Two versions of a previously developed and validated subgrouping tool for use in primary care [19] will be used. The tools include key physical and psychological predictors of outcome in LBP. A 6-item computer-based subgrouping tool will be embedded in the EMIS GP computer system, for use in real-time GP/patient consultations. Following completion, patients are categorised as either at low (a score of 2 or less) or high (a score of 3 or more) risk of poor outcome and a recommendation is made about whether or not a referral to physiotherapy is likely to be most appropriate. Patients classified as at low risk of poor outcome are recommended to receive best primary care advice and management by the GP, to include a screen for red flags, reassurance about their good prognosis, the benign nature of their pain, and simple messages and advice about pain relief, appropriate physical activity levels, return to normal activity (including work), avoiding bed rest, appropriate use of pain relieving modalities and the role of further investigations. To reinforce these key messages, a brief information sheet will be given. No onward referral to other services is recommended although patients will be advised to re-consult if symptoms persist. Patients at high risk of poor outcome are recommended to be referred to physiotherapy. The GP and patient are then able to use this recommendation in their decision-making.

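### The secondary per-protocol comparison filters phase 3 on adherence but leaves phase 1 unfiltered, so it can show a difference when there is no treatment effect

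*Protocol article*

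**What the plan says.** In the protocol article, under Data analysis, Clinical outcomes for patients, the primary analysis compares all phase 1 with all phase 3 patients on intention-to-treat principles. A per-protocol analysis "will be carried out as a secondary comparison". It takes "phase 3 patients who were treated with strict adherence to the subgrouping tool allocation rule (versus all phase 1 patients").

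Regressions are run unadjusted and also "adjusted for baseline imbalances in certain variables i.e. age, gender and baseline values of key outcomes". The reason given is the before-and-after design: "Statistical adjustment is necessary as this is an observational, before and after study design, and thus open to the possibility of confounding bias". Selection by adherence is not mentioned there, nor among the design limitations in the Discussion.

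Three other statements bear on who counts as adherent:

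- Phase 1, Patients' clinical outcomes: "There will be no subgrouping for targeted treatment in phase 1". No adherent set can be observed in phase 1.
- The sub-grouping tools and targeted treatment approaches: after the tool gives its recommendation, "The GP and patient are then able to use this recommendation in their decision-making". Following it is a choice.
- Same section, for low-risk patients: "No onward referral to other services is recommended although patients will be advised to re-consult if symptoms persist".

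**The concern.** The filter acts on one side only and depends on decisions made after the patient enters the study. Two kinds of selection follow.

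1. **Risk mix.** Low-risk care can be completed in the GP consultation. Medium- and high-risk care runs through referral, a physiotherapy visit and a second classification with the 9-item tool. Adherence is plausibly easier for low-risk patients, so the adherent set would contain more of them than the phase 1 cohort.
2. **Prognosis within risk group.** Motivated patients, or those with a better outlook for reasons not measured at baseline, may adhere more often. If a low-risk patient who re-consults with persisting symptoms and is then referred is counted as non-adherent, the exclusion depends partly on the outcome itself.

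At stake is the reading of a named secondary comparison on both primary outcomes. A reader would naturally take it as the effect when the system is actually used. The article also foresees that use of the tools may decline over the 12 months of phase 3, so the excluded share need not be small.

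**Working it through.** **Inputs from the article (Sample Size, Patients).** Expected risk mix 40/40/20% low/medium/high; SD 5; two-sided 5%; phase ratio 1:2; 1000 patients with 20% loss, so about 267 versus 533 analysed; whole-population target about 0.2 SD, or roughly 1 RMDQ point.

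**The plan's own figures.** For 50 versus 100 patients and 2.5 points, the standard error is 5 × √(1/50 + 1/100) = 0.866, and power is 82.3% (normal) or 81.8% (t), against the stated figure of about 80%. For 267 versus 533, power is 76.0% at 1.00 point and 80.0% at 1.05 points, consistent with the stated approximations. The benchmark of about 1 point is therefore sound.

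**Inputs assumed (not in the documents).** Adherence of 80-90/60-80/50-70% and 6-month RMDQ means of 3/6-7/9-11 in low/medium/high risk. No treatment effect.

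**Step 1: unadjusted risk-mix bias.** With mix p, adherence a and means m, the spurious benefit is Σpm − Σpam / Σpa.

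| Case | Adherence | Means | Phase 1 mean | Adherent mix | Phase 3 adherent mean | Spurious benefit |
|---|---|---|---|---|---|---|
| Worked example | 0.9/0.6/0.6 | 3/7/11 | 6.20 | 0.500/0.333/0.167 | 5.67 | 0.53 |
| Lowest in range | 0.8/0.8/0.7 | 3/7/9 | 5.80 | 0.410/0.410/0.179 | 5.72 | 0.08 |
| Highest in range | 0.9/0.6/0.5 | 3/7/11 | 6.20 | 0.514/0.343/0.143 | 5.51 | 0.69 |

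Cross-check by the identity bias = (1 − f) × D, where f is the adherent share and D the outcome gap between non-adherent and adherent patients. In the worked example f = 0.36 + 0.24 + 0.12 = 0.72. The non-adherent mean is (0.04×3 + 0.16×7 + 0.08×11)/0.28 = 7.57, so D = 7.57 − 5.67 = 1.90 and 0.28 × 1.90 = 0.53.

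**Step 2: what baseline adjustment does to it.** The worked example was simulated with assumed baseline RMDQ means of 4/9/14 or 5/10/15, within-group baseline SD 4, within-group outcome SD 4 or 5 and within-group baseline-outcome correlation 0.4-0.6. Adjusting for baseline RMDQ cuts 0.53 to about 0.01-0.14.

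**Step 3: selection that baseline scores do not capture.** This was a null simulation with 267 versus 533 patients, SD 5, regression adjusted for a baseline score, and adherence depending on residual prognosis through an assumed odds ratio per SD. Better prognosis was assumed to go with adherence.

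| Odds ratio | 80% adherent | 60% adherent | 40% adherent |
|---|---|---|---|
| 1 | about 0 (5% rejection) | about 0 (5%) | about 0 (6%) |
| 1.5 | 0.33 (17%) | 0.66 (45%) | 1.01 (71%) |
| 2 | 0.56 (39%) | 1.09 (87%) | 1.63 (98%) |

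Entries are spurious RMDQ benefit and the two-sided rejection rate. The all-patients comparison stayed at about 5% in every cell. By the identity, 60% adherence with non-adherers 2.5 points worse gives 0.4 × 2.5 = 1.0 point, rejected about 67% of the time.

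**The case against.** **Weight.** The analysis is explicitly secondary, and the primary comparison is clean in this respect. That stands, and limits the seriousness of the point.

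**Adjustment.** The only mechanism that can be tied to the article's own risk mix is largely dealt with by the planned baseline adjustment (Step 2). That also stands. A reader might infer from the 0.08-0.69 range that the adjusted analysis carries a bias of that size, but the range describes the unadjusted contrast only. Step 3 shows what adjustment leaves behind, but its odds ratios and adherence rates have no source in the documents and only illustrate the mechanism.

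**Direction.** A reader might infer that the comparison must favour the new system. The article does not support this. It reports no adherence rates and no working definition of strict adherence, which a full protocol may supply. If medium- or high-risk patients who recover before attending physiotherapy are counted as non-adherent, dropping them would work against phase 3. A false benefit is the likelier result, not a certain one.

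**Subgroups.** The sample-size section states aims by risk subgroup, where risk mix cannot confound. This helps only if the per-protocol analysis is run within those subgroups, which the article does not say. Selection within a subgroup would remain.

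**Conclusion.** The point holds as a design fault in one secondary analysis. As written, the per-protocol comparison selects on post-consultation adherence in phase 3 only, so it can differ from zero with no treatment effect, and nothing in the article corrects for this.

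Under the assumed adherence rates and outcome means, the unadjusted contrast carries a spurious phase 3 benefit of 0.08-0.69 RMDQ points (0.53 in the worked example). Most of that risk-mix component should disappear on adjustment for baseline RMDQ. Selection on unmeasured prognosis, motivation or post-baseline course would remain. Its size cannot be determined from the documents, and its direction probably, though not certainly, favours phase 3. The intention-to-treat result does not depend on any of this.

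**What to change.** Change the per-protocol wording as follows:

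1. Classify patients in both phases by the subgrouping tool responses in the patient questionnaire. The practitioner part of Data analysis implies that these exist before and after the intervention. Table 2 does not list the tool by name, so confirm this first.
2. Run the comparison within risk group, or standardised to the same risk mix in both phases.
3. Weight phase 3 adherers by the inverse probability of adherence given risk group, baseline RMDQ and catastrophising, age, gender, pain duration and practice, so that they represent all phase 3 patients.
4. Add a sensitivity analysis for unmeasured selection, for example by varying D in (1 − f) × D with the observed f. The weights handle measured predictors only.
5. Label the result exploratory, and draw no causal conclusion from the unadjusted contrast.

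Using phase as an instrument for a complier effect is not a good substitute. The phase 2 programme changes GP care beyond use of the tool (imaging, advice, activity, sickness certification), and the Discussion concedes that other influences may change outcomes over time.

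The cost is one extra model on data already planned for collection, and a slightly wider interval.

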**Figure 1 F1:**
[figure not shown]
Summary of IMPaCT Back study design

We considered using a clinical trial design with cluster randomisation at the level of GP practice. However, the physiotherapy service is PCT based rather than GP practice based, which would have been likely to lead to contamination of clusters.

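### The primary phase 1 v phase 3 regressions leave out practice, although the same 7 practices supply both phases and deliver the new system

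*Protocol article*

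**What the plan says.** Under Data analysis, Clinical outcomes for patients, the phase 1 v phase 3 estimates, "with 95% confidence intervals will be calculated using linear regression (for numerical outcomes) and logistic regression (for categorical outcomes"), are to be produced unadjusted and adjusted. The adjustment list is introduced as a definition rather than as examples: age, gender and baseline values of key outcomes. The same section says adjustment is needed because a before-and-after comparison is open to confounding. The preceding section, on practitioners' behaviour and care processes, treats the patient-based process measures as unmatched and analyses them with unpaired t-tests, chi-square tests and the same regressions.

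Under Sample Size, Patients, the study "has 80% power to detect a 'small' effect size of about 0.2, equivalent to a mean difference in RMDQ scores of approximately 1", after 20% loss to follow-up. No clustering allowance is mentioned there.

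Four other places bear on this:
- Study Design: "We considered using a clinical trial design with cluster randomisation at the level of GP practice". This was rejected because the physiotherapy service is organised across the Primary Care Trust.
- Health care practitioners' eligibility criteria: practices are selected for a spread of setting and size.
- Phase 1 and Phase 3 patient sections: each participating practice recruits consecutive patients in both phases.
- Multi-component quality improvement intervention: training, feedback and the computer prompt are delivered practice by practice.

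**The concern.** There are two separate problems.

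**Confounding.** Entry to the study depends on the GP entering a Read Code, raising the study with the patient and not opting out of the prompt. If some practices do this more readily in one phase than in the other, the practice mix differs between phases. Practices chosen to differ in setting and size may also differ in outcome. Practice is known for every patient, but it is missing from an adjustment list whose stated purpose is to deal with confounding. The per-protocol comparison is more exposed, because it sets adherent phase 3 patients against all phase 1 patients, and practices with high adherence will then weigh more on one side.

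**Standard error.** The regressions treat patients as independent. Because practice is crossed with phase, the effect can go either way. A stable practice effect cancels from the contrast, and the planned standard error is then a little too large. If practices change by different amounts, it is too small. Uneven change is foreseeable: the extra practice meetings depend on availability, the additional educational sessions are only offered, and the article expects that use of the tool may fall over time.

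At stake are the intervals and p-values for both primary outcomes, for the secondary outcomes and for the process measures.

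**Working it through.** **Inputs from the article.** 1000 recruited; 20% loss; phase ratio 1:2; SD 5 RMDQ points; 7 practices; two-sided 5% (stated for the subgroup calculation and taken to carry over to the total population).

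**Assumed inputs.** ICC 0.01 to 0.05 and between-phase correlation of practice effects (c) 0.5 to 1. The article gives neither.

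**1. The plan's own power figures.**
- Subgroup, 50 v 100, 2.5 points, SD 5: 2.5 / (5 × √(1/50 + 1/100)) = 2.887. Power = Φ(2.887 − 1.960) = 82.3%. The article says "is powered at about 80% to detect a 2.5 point difference, assuming a standard deviation of 5", which agrees.
- Total population: 1000 × 0.8 = 800, split 1:2 into 267 v 533. The variance factor is b = 1/266.7 + 1/533.3 = 0.005625, so √b = 0.075.
- Effect detectable with 80% power: (1.960 + 0.842) × 0.075 = 0.210 SD, or 0.210 × 5 = 1.05 points. This agrees with the rounded effect size and mean difference in the article.

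**2. Clustering with practice crossed with phase.** The parallel-cluster factor 1 + (m − 1) × ICC does not apply, because every practice is in both phases. With 7 equal practices:

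variance of the phase difference (in SD²) = (1 − ICC) × b + 2 × ICC × (1 − c) / 7

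Design effect (DE) = that variance / b. The planned test assumes DE = 1, so its true type I error is 2 × [1 − Φ(1.96 / √DE)].

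| ICC | c | DE | Type I error of planned test | Power at 0.2 SD, correct variance |
|---|---|---|---|---|
| 0.01 | 1 | 0.99 | 4.9% | 76% |
| 0.01 | 0.8 | 1.09 | 6.1% | 72% |
| 0.01 | 0.5 | 1.24 | 7.9% | 67% |
| 0.05 | 1 | 0.95 | 4.4% | 78% |
| 0.05 | 0.8 | 1.46 | 10.5% | 60% |
| 0.05 | 0.5 | 2.22 | 18.8% | 43% |

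Worked case (ICC 0.05, c 0.5): 0.95 × 0.005625 + 2 × 0.05 × 0.5 / 7 = 0.005344 + 0.007143 = 0.012487. DE = 0.012487 / 0.005625 = 2.22, and 1.96 / √2.22 = 1.315, giving 18.8%.

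The power column uses the normal critical value 1.96. With no clustering, power at exactly 0.200 SD is Φ(0.2/0.075 − 1.96) = 76.0%.

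**3. Price of a model with practice-by-phase variation.** Seven practices leave about 6 degrees of freedom for the phase contrast. The critical value is t(0.975, 6) = 2.45 instead of 1.96, and 2.45 / 1.96 = 1.25, so intervals are about 25% wider even with no clustering. Power at 0.2 SD (noncentral t, noncentrality 0.2/0.075 = 2.67) then falls from 76% to about 61%. At ICC 0.05 and c 0.5 it is about 33%.

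**4. Practice-mix confounding.** The article has no figures by practice, so this bias cannot be sized.

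**The case against.** **Stable practice effects cancel.** The same practices appear in both phases, and if their effects are stable the planned test is slightly conservative. This stands. A reader might infer that the intervals and p-values are simply invalid. The article does not support that: the direction depends on a between-phase correlation it does not give, and the 19% needs the least favourable ICC and correlation of the assumed range together.

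**Full documents not shown.** An analysis plan could add a practice term or robust standard errors. This stands in part. But the article does name a model and defines its covariates, and practice is not among them.

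**Mix shift not shown.** Phase 3 recruitment follows the phase 1 procedures, and baseline adjustment may absorb part of any difference between practices. True. The case for adding practice rests on its negligible cost, not on a demonstrated bias.

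**A random practice-by-phase model is a choice, not a correction.** The practices were selected for breadth within one Trust, so inference conditional on them is defensible. The random term generalises to other practices and is expensive with 7 of them. It also misses clustering by physiotherapist, because that service is not organised by practice. This stands, and it is why that model belongs in a sensitivity analysis.

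**The power figure.** A reader might infer that the stated 80% is really 76%, or that an equal split was used by mistake. Neither follows. The 76% arises only if the rounded effect is read as exactly 0.200. At 267 v 533, 80% power corresponds to 0.21 SD and 1.05 points, which fits the article's "effect size of about 0.2, equivalent to a mean difference in RMDQ scores of approximately 1, over the total study population". The 1:2 split reproduces the claim to the precision given.

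**Conclusion.** The point holds for the analysis model. As written, the primary regressions and the patient-based process comparisons omit practice and treat patients as independent, in a study where practice is a known structural variable and the route of delivery. Two consequences follow: possible confounding by practice mix, of unknown size, and a standard error that may be wrong in either direction. Under the assumed ICC of 0.01 to 0.05 and between-phase correlation of 0.5 to 1, with 7 equal practices, the design effect is 0.95 to 2.2 and the type I error of the planned test about 4.4% to 19%. This is a worthwhile correction at small cost, not proof that the planned results would be wrong. The power statement is arithmetically sound for independent patients; it only needs to say that it makes that assumption.

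**What to change.** 1. In Data analysis, Clinical outcomes for patients, add practice as a fixed effect to every phase 1 v phase 3 contrast, including the per-protocol comparison. Do the same for the patient-based regressions in the section on practitioners' behaviour and care processes.
2. Report a sensitivity analysis for the primary outcomes that allows practice-by-phase variation with small-sample degrees of freedom. The fixed effect deals with practice mix and stable practice differences, but not with practices changing by different amounts. State in advance that, with 7 practices, this analysis gives clearly wider intervals (critical value about 2.45 instead of 1.96).
3. In Sample Size, Patients, note that the power figure assumes independent patients. Keep the 80% figure and the recruitment target.

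**Cost.** Item 1 uses six degrees of freedom out of about 800 patients and needs no new data. Item 2 has low power (about 61% at 0.2 SD even without clustering), so a wide interval there should not be read as contradicting the main analysis. Item 3 is one sentence.
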